## Randomization

Participants are randomly assigned to the intervention and comparison groups. After meeting the inclusion criterion and obtaining informed consent block randomization is used. Computer-generated random numbers is assigned which have been pre-assigned to one of the two groups (intervention and comparison). The random numbers corresponding to either group has been sealed in an envelope numbered sequentially. The sealed envelope is opened after obtaining the informed consent. Until opening of the envelope, neither the participants nor the healthcare provider is aware of the group that they are assigned to. The envelope that contained “A” meaning “Intervention group” and the envelope contained “B” meaning “Comparison group”.

## Study site

There are substantial numbers of health care centres in any district level in Bangladesh provided by the government, non-governmental organization (NGOs), private providers etc. For this study a government running Maternal & Child welfare Centre (MCWC) is selected in Chandpur district. This municipality area of Chandpur has a population of 94,821 with 49.23% women population. Among the total registered pregnant women, 98% received 1st ANC but only 7% of pregnant women received 4th ANC from qualified health care provider in this municipal [20]. Intervention and comparison are selected in same health centre because it serves similar populations with regard to socio-demographic factors.

## Intervention

Before designing the intervention a small piloting has carried out to observe how the group prenatal care (GPC) will be accepted in real field or not. The experience from the piloting has summarized and necessary adjustment of the intervention was carried out. Before starting the intervention, necessary trainings and workshops was conducted for the team members (group moderator, study nurse and support staffs) to improve their knowledge and skills and for making the common understanding about the GPC since skills of educators are the key of success of such intervention. After the completion of training and workshop, one or two discussion sessions has conducted for clearing their roles and their understanding about the GPC to find if there is any gap Fig. 2.

**Fig. 2 Fig2:**
[figure not shown]
Intervention flow chart

## Intervention flow chart

### Procedure to implement GPC model

Pregnant women in selected health centre are informed about the study at the booking visit or during registration. The study objectives and procedure of intervention explained clearly to the pregnant women and their husbands/guardians or accompanied persons by the project team. They informed about the content, description of the procedure and potential benefit for the enrolment of the study. Written informed consent was taken from the participants as well as their guardian prior to the study.

### Formation of group for the intervention

Each group consisted of 6 to 10 women. They met 4 to 6 times throughout the pregnancy period. Groups were formed considering the gestational age of the women. Each session continue up to two hours. The entire GPC sessions are held in separate rooms with presence of pregnant mothers of intervention group. It can reduce the likelihood of mixing with other pregnant mothers.

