## Conceptual framework

In group prenatal care, prenatal assessment, education and skills development will be occurred in an atmosphere that facilitates learning, encourages free exchange, and develops mutual support [17]. Group care will permit more time for pregnant women to develop a relationship among each other and to discuss recommended content of care. Peer education approaching (i.e. through peer participation) maternal health promotion will be carried out through peer educators like current pregnant women and experienced mothers. It is expected that group care with peer education will increase interaction with each other of the group members that can encourages women to utilize their knowledge through skill building which may improve their recommended healthcare utilization throughout the pregnancy period. Women thus are better able to take control of their adverse health situation during prenatal and postnatal period Fig. 1.

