## Sample size

The sample size is estimated using the technique proposed by [18, 19] for comparing two independent proportions. To calculate the sample sizes for detecting difference between intervention and comparison groups, following formula has been employed$$ \mathrm{n}=\frac{{\left[\ {\mathrm{Z}}_{\upalpha}\sqrt{\left(\mathrm{r}+1\right)\overline{\mathrm{P}}\overline{\mathrm{Q}}}+{\mathrm{Z}}_{\upbeta}\sqrt{\Big({\mathrm{r}\mathrm{P}}_1{\mathrm{Q}}_1+{\overline{\mathrm{P}}}_2{\overline{\mathrm{Q}}}_2}\ \right]}^2}{{\mathrm{r}\updelta}^2} $$

Where,

a) $$ \updelta =\left|{\mathrm{P}}_2-{\mathrm{P}}_1\right| $$, b) $$ \overline{\mathrm{P}}=\frac{{\mathrm{P}}_1+\mathrm{r}{\mathrm{P}}_2}{\mathrm{r}+1} $$, c) $$ \overline{\;\mathrm{Q}}=1-\overline{\mathrm{P}} $$

d) α, the probability of type I error,e) β, the probability of type II error, or (1-power of the test)

f) P_1_, proportion of characteristic present in intervention group, g) P_2_, proportion of characteristic present in comparison group d) r, ratio of required sample size from two groups (*r* = 1 in this study)

It is expected that due to intervention different types of indicators (Table 1) will change. Using this percentage of expected change difference in intervention and comparison groups at 5% error level and 80% power the estimated sample size for each group is reported in following table. The highest sample size (250) is estimated for breastfeeding rate. Considering the 15% lost to follow-up, the sample size is 288 for each group. Therefore, in total 576 pregnant women (288 cases and 288 comparisons) will be enrolled randomly in this study. Recruitment will take place from May 20, 2015 to May 30, 2016 and intervention was completed on October 30, 2016. Data collection is ongoing now among the enrollees.

**Table 1 Tab1:** Sample size estimation

Indicators	Parentage	% of expected change	Required sample size	Sample size (15% lost to follow-up rate)	Total sample
ANC^1^	55.0%	14%	202	232	464
PNC^1^	27.0%	15%	170	196	392
Skilled-birth attendance^1^	31.7%	16%	158	182	364
Institutional deliveries^1^	28.8%	13%	227	261	522
Preterm birth^2^	22.30%	−12%	164	189	378
Low birth weight^3^	36%	−12%	245	282	564
Postpartum complications	36%	−13%	208	239	478
Breastfeeding rate (2–3 m)^1^	71.0%	11%	250	288	576

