## Data analysis

The analysis of quantitative data will be based on a before and after assessment of the selected indicators, calculation of changes, and statistical significance based on 95% confidence intervals and other standard significance tests. Independent sample *t*-test for mean and proportion will be performed to test significance of difference in outcome variables between intervention and comparison group. To examine the normality of continuous outcome variable (like, low-birth-weight) histogram will be drawn. If the outcome variable found non-normally distributed, non-parametric test method (like, Kruskal–Wallis) will be employed. Advanced statistical techniques (such as multivariate regression analyses), will be used to document the net effects of the interventions on the outcome indicators after controlling for the individual-level socioeconomic factors. Data analysis will be done by using STATA 13.0.

For qualitative data analysis, content analysis will be done manually with qualitative information obtained through in-depth interviews. Immediate after the interview, the interviewers will complete the field-notes and transcribe the recording. After transcribing the interview, they will read the transcript carefully to identify potential themes. After then coding of data will begin through identifying possible themes and sub-themes.

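### Women in the GPC arm are treated in groups of 6 to 10, but the sample size and the named tests make no allowance for within-group correlation

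*Protocol article*

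**What the plan says.** The Randomization section allocates individual women by sealed envelope. Under Formation of group for the intervention, GPC women then meet 4 to 6 times in groups formed by gestational age: "Each group consisted of 6 to 10 women". The Research design and methods section gives the comparison arm individual care, so treatment groups exist in one arm only.

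The Conceptual framework expects group care with peer education to "increase interaction with each other of the group members" and, through that, to improve use of recommended care.

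The Sample size section uses a formula "for comparing two independent proportions" and reports, "at 5% error level and 80% power the estimated sample size for each group", with no ICC or design effect. It states: "The highest sample size (250) is estimated for breastfeeding rate". Adding 15% for loss gives 288 per arm.

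The Data analysis section says that an independent-sample t-test for means and proportions "will be performed to test significance of difference in outcome variables between intervention and comparison group". It adds a rank test for non-normal outcomes and multivariate regression controlling for individual-level socioeconomic factors. It mentions no group effect or cluster-robust error.

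**The concern.** This is an individually randomised group-treatment trial, nested in one arm. Women who share sessions and are meant to influence each other may have more similar outcomes than women in different groups. If so, 250 GPC women carry less information than 250 independent women, while the comparison arm is unaffected.

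Two things follow. A test that ignores the grouping uses too small a standard error, so its confidence intervals are too narrow and it rejects a true null more often than 5%. A test that respects the grouping has less power than Table 1 implies. The stated alpha and power therefore cannot both hold for an outcome with positive within-group correlation and no spare power. The Discussion links scale-up to success, and the error makes a difference easier to declare.

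**Working it through.** **Inputs from the article.** Group size m = 6 to 10, so 288 GPC women form between 288/10 = 28.8 and 288/6 = 48 groups (36 at m = 8). Alpha is 5%, power 80%, allocation 1:1. The breastfeeding row of Table 1 reads "71.0% 11% 250 288 576", that is 71% against 82%.

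**Assumptions.** ICC 0.01 to 0.10 (none is given); mean group size 8, with 6 and 10 as limits; equal group sizes; two-sided test (sidedness is not stated, but two-sided reproduces the table).

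**Step 1: reproduce the plan's figure.** For breastfeeding, mean proportion 0.765, difference 0.11:

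n' = [1.96·√(2·0.765·0.235) + 0.8416·√(0.71·0.29 + 0.82·0.18)]² / 0.11² = (1.1753 + 0.5004)² / 0.0121 ≈ 232.1, so 233 by the printed formula.

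With a continuity correction: n = (n'/4)·[1 + √(1 + 4/(n'·0.11))]² ≈ 249.9, so 250 as stated.

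The same corrected method reproduces all eight rows exactly (202, 170, 158, 227, 164, 245, 208, 250), so no allowance for groups is hidden in them. Then 250 × 1.15 = 287.5, giving 288.

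**Step 2: design effect, GPC arm only.** DE = 1 + (m − 1)·ICC. At m = 8: 1.07, 1.14, 1.35 and 1.70 at ICC 0.01, 0.02, 0.05 and 0.10.

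**Step 3: true type I error of the test that ignores groups.** With equal arms under the null, the correct variance is (1 + DE)/2 times the naive one, so

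α = 2·[1 − Φ(1.96·√(2/(1 + DE)))].

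At ICC 0.05, m = 8: 1.96·√(2/2.35) = 1.808, so α ≈ 7.1%.

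| ICC | m = 6 | m = 8 | m = 10 |
|---|---|---|---|
| 0.01 | 5.3% | 5.4% | 5.5% |
| 0.02 | 5.6% | 5.8% | 6.0% |
| 0.05 | 6.5% | 7.1% | 7.7% |
| 0.10 | 8.0% | 9.2% | 10.4% |

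These are for the uncorrected test.

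**Step 4: power of a test that allows for groups.** Table 1's continuity-corrected method, 250 evaluable per arm, DE on the GPC variance only:

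power = Φ[(δ − c − 1.96·SE₀)/SE₁], c = ½(1/250 + 1/250) = 0.004.

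Breastfeeding, ICC 0.05, m = 8: SE₀ = √(0.765·0.235·2.35/250) = 0.0411; SE₁ = √[(0.82·0.18·1.35 + 0.71·0.29)/250] = 0.0403; (0.106 − 0.0806)/0.0403 ≈ 0.63, so power is 73.6%.

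| Outcome (m = 8) | ICC 0 | 0.01 | 0.02 | 0.05 | 0.10 |
|---|---|---|---|---|---|
| Breastfeeding | 80.0% | 78.7% | 77.4% | 73.6% | 67.7% |
| Low birth weight | 81.0% | 79.7% | 78.4% | 74.6% | 68.7% |
| Institutional delivery | 84.1% | 82.8% | 81.5% | 77.7% | 71.8% |
| Postpartum complications | 87.3% | 86.2% | 85.1% | 81.8% | 76.4% |
| ANC | 88.2% | 87.1% | 86.0% | 82.8% | 77.4% |
| PNC | 93.2% | 92.4% | 91.5% | 88.8% | 84.0% |
| Preterm birth | 94.2% | 93.6% | 92.9% | 90.8% | 86.9% |
| Skilled attendance | 94.8% | 94.1% | 93.4% | 91.0% | 86.7% |

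At ICC 0.05 breastfeeding is 75.4% at m = 6 and 71.9% at m = 10.

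**Step 5: evaluable women per arm for 80% on breastfeeding (m = 8).** 258, 266, 289 and 328 at ICC 0.01, 0.02, 0.05 and 0.10, against 250.

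**The case against.** **The size is unknown.** Without an ICC, only the direction is certain, and only if the ICC is positive. At 0.01 the type I error is about 5.4% and breastfeeding loses just over one point of power. This stands.

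**Without a continuity correction there is some slack.** At 250 per arm breastfeeding then starts at 82.9% and stays at 80% or above until the ICC reaches about 0.033, 0.023 or 0.018 for groups of 6, 8 or 10. A reader might infer that the trial simply fails to deliver 80% power. The article does not support that as a general statement: five of the eight sized outcomes keep 80% at ICC 0.05, including three of the four service-coverage outcomes named in the abstract.

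**Not every primary outcome need be affected.** The stated mechanism concerns interaction, knowledge and use of care. It makes correlation plausible for utilisation and breastfeeding, but gives no direct reason to expect much in birth weight or gestational age. A reader might also blame a shared moderator, but the article describes one centre and does not say that moderators differ between groups. If the same staff ran every group, they would not create differences between groups. Both stronger readings should be dropped.

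**Attrition is a separate matter.** If 15% of 288 are lost, 288 × 0.85 ≈ 245 remain and breastfeeding power is already 79.2% at ICC 0. That point comes from the inflation method, so the working uses the planned 250.

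**An unseen analysis plan might supply the right model.** It might. But the article names tests for independent observations and fixes a sample size under independence, and a later plan would not change that calculation.

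**Conclusion.** The point holds in a limited form. The article's own design puts women into treatment groups in one arm and relies on interaction within them, while its sample size and named tests assume independence. For any outcome with a positive within-group ICC, the planned p-values and intervals are anti-conservative. At ICC 0.02 to 0.05 and m = 8 the excess type I error is modest (5.8% to 7.1%); at 0.10 it approaches double the nominal level.

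The loss of power matters mainly for breastfeeding, which has no spare power by Table 1's own method, then for low birth weight and institutional delivery. ANC and postpartum complications drop below 80% only towards ICC 0.10; PNC, skilled attendance and preterm birth stay above it throughout the range at m = 8. Caesarean delivery is listed as primary but is not in Table 1, so its power cannot be assessed here.

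These figures rest on the assumed ICC range, equal group sizes and normal approximations. Loss to follow-up would shrink an average group of 8 to 8 × 0.85 = 6.8, which is inside the 6 to 10 range shown.

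**What to change.** In Data analysis, replace the independent-sample tests by a partially nested analysis. Take GPC group as the cluster in the intervention arm and each comparison woman as a cluster of one. Use a mixed model with the group effect in the GPC arm only, or cluster-robust standard errors with a small-sample correction, since only about 29 to 48 groups are expected. Apply the same structure to the adjusted regressions, and report the observed ICC for each outcome.

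In Sample size, restate power for each outcome with the design effect in the GPC arm only, over an assumed ICC range of 0.01 to 0.10. Applying it to both arms would overstate the loss.

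The cost is small: keep the group number on each GPC woman's record and change a few lines of analysis code. Intervals become somewhat wider and stated power lower. No more women are needed for valid inference, although recovering 80% for breastfeeding would have required the larger numbers in step 5.

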### Conduct sessions within group

The intervention consists of group sessions, providing BCC materials and regular follow-up to the participants. In each session starts after individual physical assessment of women by the qualified healthcare provider of the facility. The group discussions take 30–40 min and focuses sequentially on education and skills-building specific to prenatal and postnatal care with the help of study nurse. Session themes include the prenatal nutrition, common discomforts of pregnancy, caring of mother’s health during pregnancy, pregnancy danger signs, decisions of pregnancy care, developing a birth plan, breastfeeding, postpartum adjustment, medical procedures and tests during pregnancy and new baby care. In addition, key messages focused on maternal, neonatal and child health provides through leaflets to the intervention group.

### Follow up of the participants

Detailed information of registered women including address and phone number are taken for communication. Mobile follow-up is carried out regularly to track all of the participants.

## Cost of intervention

Incremental Cost i.e. the additional costs those will be used over the existing facilities for implementing group prenatal care intervention in these facilities will also be calculated. For calculating the incremental cost of introducing GPC, ingredient method will be applied which comprises, listing all types of inputs by activity and the quantities and prices for each input [21]. Both recurrent and capital cost will be included in the total cost. However, fixed cost and variable cost will be captured and presented separately. Capital cost will be annuitized and adjusted for inflation-adjusted discounting rate. With the discounting the present values of all costs will be calculated taking into account of the time when these costs will be incurred with their opportunity costs [22]. If the cost and outcome will take in different year, then 5% discount rate will be used.

Incremental cost-outcome ratio will be calculated i.e. if we switch one alternative to another alternative, the change in cost and outcome will be compared. Change in various effects between intervention and comparison group due to introducing GPC will be considered as the change in outcome/success of the intervention.

## Qualitative assessment

As the nature of the project is participatory, the qualitative evaluation will be conducted. The proposed study can obtain valuable information about the experience of the mother from GPC. Throughout the project period qualitative data collection such as conducting interview with mothers (in-depth interview) will be done to explore the perception and experience of mothers, expressed needs, health providers’ interactions and skills, institutional inadequacies, needs and benefits of women friendly GPC.

## Method of data collection

### Quantitative data

This study is prospective in nature and follow up of participants will be done from early pregnancy through 2 months postpartum. Both structured and semi-structured questionnaire will be used for data collection. Data will be collected at two points of time: 24 h after delivery, and 2 months after delivery. Cost data will be collected through structured and semi-structured questionnaire, observation checklist, hospital database and compilation of service statistics. Gestational age at birth, birth weight, neonate hospital stay, and maternal outcomes will be taken from medical records in hospitals and health centres, and individual structured interviews. Review of medical records and structured interviews will be carried out by trained study nurses.

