## Background

There is growing concern about prenatal care for women especially in developing countries, where 80% of the world’s women live [1]. Approximately ninety-nine percent of maternal and neonatal deaths occur in developing countries which is higher in rural areas and among poorer communities [2]. There is an immediate need for implementation of evidence-based, cost-effective interventions to improve maternal and neonatal health outcomes [3]. The Government of Bangladesh is committed to achieving Millennium Development Goal (MDG) 4 and 5; to reduce the under-5 mortality ratio from 146 per 1000 live births in 1990 to 48 per 1000 live births in 2015 and to improve maternal health, by reducing the maternal mortality ratio from 574 to 143 deaths per 100.000 live births by 2015 respectively.

However, the antenatal care (ANC) and postnatal care (PNC) received by medically trained provider is still very low and around 55 and 27% respectively [4]. Although the current practice of the safe motherhood programmes in Bangladesh is to advice pregnant women to deliver their babies in facilities but almost 62% are performed at home (BDHS 2014). Further, though breastfeeding initiation within one hour after birth has increased over time, still it remains below 50% [5]. Despite a fair amount of advocacy around maternal and newborn care, real progress on the ground remains slow [6]. Further efforts are needed to ensure better coverage of antenatal care, as well as improved quality and content of this care [7].

Major causes of maternal death are largely haemorrhage (31%), eclampsia (20%), and abortion (15%) in Bangladesh [5, 7]. Pregnant women are advised to seek care from a medically trained provider or from a facility when they experience complications during pregnancy, at delivery, or postpartum period till 42 days. There are some BCC activities on birth planning and certain danger signs that women may encounter during pregnancy, at delivery, or during postpartum period but the progress is still slow.

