### Inclusion criteria for participants

Potential participants for either group are to be pregnant women with less than 20 weeks of gestational age, between the age of 18 and 42, without medical complications like pregnancy with jaundice, heart disease, asthma, diabetes, and willing to participate in this study.

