## Outcome of the study

### Primary outcome

Primary outcomes will include ANC and PNC coverage, skilled birth attendance and institutional deliveries, low birth weight (<2500 g), preterm birth, caesarean delivery, postpartum complications and breastfeeding rate (2 months postpartum). It is expected that due to GPC some outcome variables like ANC, PNC, skilled birth attendance, institutional deliveries and breastfeeding rate will be improved.

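### Birth weight and gestational age at birth come from facility records and interviews with no common method for all births, so the source mix for two primary outcomes would shift with facility delivery, which GPC is meant to raise

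*Protocol article*

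**What the plan says.** Under Primary outcome, the protocol article lists LBW (below 2500 g) and preterm birth among nine primary outcomes. Under Method of data collection, Quantitative data, it states: "Gestational age at birth, birth weight, neonate hospital stay, and maternal outcomes will be taken from medical records in hospitals and health centres". The sentence goes on to add interviews, so the values "will be taken from medical records in hospitals and health centres, and individual structured interviews". The same section adds: "Review of medical records and structured interviews will be carried out by trained study nurses". On timing it says: "Data will be collected at two points of time: 24 h after delivery, and 2 months after delivery". The article does not say which source takes precedence, and it mentions no weighing by study staff.

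Three other places bear on this:
- The Background says of births in Bangladesh that "almost 62% are performed at home (BDHS 2014").
- Table 1 under Sample size plans for institutional delivery of 28.8% with an expected change of 13 points, and Primary outcome expects that "institutional deliveries and breastfeeding rate will be improved".
- Inclusion criteria for participants admits "pregnant women with less than 20 weeks of gestational age", so each pregnancy must be dated at enrolment, before the place of delivery is known.

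**The concern.** The two named sources differ in quality. A facility record can hold a weight taken at birth. An interview gives what the mother or family can report. For a home birth, the interview is normally the only listed source left for birth weight. By the protocol's own figures most births are at home, and the intervention is intended to reduce that share.

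The source of one primary outcome therefore tends to follow another primary outcome that is determined after randomisation and that GPC is expected to alter. Randomisation does not protect against this, and neither does using the same nurses and contacts in both arms. Two things are at stake: a false difference in LBW when GPC has no effect on it, and a true effect that is watered down so that the planned sample no longer has its intended power.

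**Working it through.** **Inputs from the protocol article (Table 1)**
- Institutional delivery: 28.8% comparison; 28.8 + 13 = 41.8% GPC.
- LBW: 36% comparison; 36 - 12 = 24% GPC. Preterm birth: 22.3% and 10.3%.
- Largest required size: 250 evaluable women per arm.

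**Assumptions (not in the documents)**
- Interview sensitivity 0.5 to 0.8 and specificity 0.8 to 1.0 for LBW in home births.
- Facility records are correct, and true risk is the same at home and in a facility.

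**1. The plan's own figure.** For LBW, two-sided 5% and 80% power:
n = [1.96√(2 × 0.30 × 0.70) + 0.842√(0.36 × 0.64 + 0.24 × 0.76)]² / 0.12² = 228 per arm, and 245 with a continuity correction. The latter matches Table 1. The same method gives the tabulated 227 for institutional delivery. These sizes are not in dispute.

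**2. Source mix.** With 250 per arm:
- Comparison: 250 × 0.288 = 72 facility births, 178 home.
- GPC: 250 × 0.418 = 104.5 facility births, 145.5 home.

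**3. Observed rate.** For true rate p and facility share f:
observed = f × p + (1 - f) × [sens × p + (1 - spec) × (1 - p)].

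**4. No true effect.** GPC minus comparison reduces to
0.13 × [p(1 - sens) - (1 - spec)(1 - p)].
For example, at 0.5 / 1.0: 0.13 × 0.36 × 0.5 = +2.3 points. At 0.8 / 0.8: 0.13 × (0.072 - 0.128) = -0.7 points.

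**5. True effect of -12 points.** At 0.5 / 1.0:
- Comparison: 0.36 × (0.288 + 0.712 × 0.5) = 23.2%.
- GPC: 0.24 × (0.418 + 0.582 × 0.5) = 17.0%.
- Difference: -6.2 points.

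LBW results at the four corners of the assumed range, 250 per arm:

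| Sens / spec | Shift under null (points) | Type I error | True -12 appears as | Power |
|---|---|---|---|---|
| 1.0 / 1.0 | 0 | 5.0% | -12.0 | 84% |
| 0.8 / 1.0 | +0.9 | 5.6% | -9.7 | 69% |
| 0.8 / 0.8 | -0.7 | 5.3% | -9.9 | 64% |
| 0.5 / 1.0 | +2.3 | 9.4% | -6.2 | 40% |
| 0.5 / 0.8 | +0.7 | 5.3% | -6.4 | 35% |

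**6. Where the dilution comes from.** If both arms had 28.8% facility births, the observed effect would be -12 × [0.288 + 0.712 × (sens + spec - 1)]. That is -6.0 points at 0.5 / 0.8 and -10.3 at 0.8 / 1.0. Most of the dilution thus comes from the large home-birth share in both arms, not from the 13-point gap.

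**7. Using the Background figure.** With 62% home births (38% facility against 38 + 13 = 51%), the shift under the null is unchanged, because it depends only on the 13-point gap. The diluted effect becomes -6.7 to -10.4 points.

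**8. Preterm birth.** If interview-based gestation had the same accuracy, the null shift would run from 0.13 × (0.223 × 0.2 - 0.2 × 0.777) = -1.4 points to 0.13 × 0.223 × 0.5 = +1.4 points. This applies only if gestational age at birth rests on the delivery record or on recall.

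**The case against.** **The source rule is inferred.** No sentence says that records are used for facility births and interviews for the rest. Both sources are named for all women, with the same nurses and the same two contacts. This stands, so a reader who infers that LBW and preterm birth are measured differently in the two arms goes too far. The methods are the same. Their mix would differ, and only if GPC raises facility delivery.

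**The direction is not fixed.** A reader might infer that more facility delivery must make LBW look more frequent under GPC. That needs high interview specificity. At sensitivity 0.8, the LBW shift turns negative once specificity falls below 1 - 0.36 × 0.2 / 0.64 = 0.89.

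**Records-only power fits no stated analysis.** Using only facility births (72 against about 104) would give about 41% power for LBW and 58% for preterm birth. But the article says that interviews will supply data and nowhere restricts the analysis to recorded values. Those figures show only why such a restriction should be avoided.

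**Preterm birth is less exposed.** All women enrol before 20 weeks at one centre, and the named health-centre records could include its antenatal record. This stands in part: the article does not say that enrolment dating is used for gestational age at birth.

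**An article condenses.** A source order or weighing procedure may be in the full protocol or a manual, and its absence here is no fault in itself. The point rests on what the article does state: two sources of different quality for these outcomes, alongside a planned change in where births occur.

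**Conclusion.** The concern holds in a limited form. As stated, the measurement plan lets the mix of recorded and interview-based values follow place of delivery, which GPC is meant to change. This affects LBW and, less strongly, preterm birth: two of the nine listed primary outcomes.

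For LBW, the false difference under the null is about -0.7 to +2.3 points, small beside the planned 12 points and of uncertain sign. Dilution matters more: a true -12 points would appear as about -6 to -10, with power of about 35% to 69% at 250 per arm instead of 84%. These figures rest on the Table 1 rates, the assumed accuracy range, error-free facility records, and equal true risk at home and in a facility. The documents supply no accuracy figures, so the range illustrates the problem and does not estimate it. It is worth acting on but does not undermine the trial as a whole.

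**What to change.** 1. **Gestational age.** For every woman in both arms, define gestational age at birth as gestational age recorded at enrolment plus the days from enrolment to the birth date. Do not use the delivery record or recalled gestation. The enrolment value is already needed for eligibility, so the rule adds no data collection. Its downside is that enrolment dating has its own error, which should be equal in the two arms.
2. **Birth weight.** Record the source and timing of each value. Report completeness and source by arm and by place of birth. Do not restrict the main analysis to facility-recorded weights. Add a sensitivity analysis over assumed interview sensitivity and specificity, as in the table above. The cost is one or two data fields and a little more analysis.

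Two other remedies are tempting but not recommended here. Weighing every newborn at the 24-hour contact assumes a visit in person, which the article does not state. Multiple imputation by arm and place of birth would have few or no recorded weights in the home-birth cells to draw on.
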